## Abstract

**Background:**

Reproductive-aged women are a high-risk population group for accelerated weight gain and obesity development, with pregnancy recognized as a critical contributory life-phase. Healthy lifestyle interventions during the antenatal period improve maternal and infant health outcomes, yet translation and implementation of such interventions into real-world health care settings remains limited.

**Objective:**

We aim to generate key implementation learnings to inform the feasibility of future scale up and determine the effectiveness of intervention delivery methods on engagement, experience, acceptability, knowledge, risk perception, health literacy, and modifiable weight-related health behaviors in women during preconception, pregnancy, and postpartum periods.

**Methods:**

This randomized hybrid implementation effectiveness study will evaluate the penetration, reach, feasibility, acceptability, adoption, and fidelity of a healthy lifestyle intervention (OptimalMe) implemented into, and in partnership with, private health care. Individual health outcomes associated with implementation delivery mode, including knowledge, risk perception, health literacy, self-management, and health behaviors, are secondary outcomes. A total of 300 women aged 18 to 44 years, who are not pregnant but wish to conceive within the next 12 months, and with access to the internet will be recruited. All participants will receive the same digital lifestyle intervention, OptimalMe, which is supported by health coaching and text messages during preconception, pregnancy, and postpartum periods. We will use a parallel 2-arm design to compare telephone with videoconference remote delivery methods for health coaching. Methods are theoretically underpinned by the Consolidated Framework for Implementation Research and outcomes based on the Reach, Engagement, Adaptation, Implementation and Maintenance framework.

**Results:**

The study was approved on August 16, 2019 and has been registered. Recruitment commenced in July 2020, and data collection is ongoing. Results are expected to be published in 2022.

**Conclusions:**

The study’s design aligns with best practice implementation research. Results will inform translation of evidence from randomized controlled trials on healthy lifestyle interventions into practice targeting women across preconception, pregnancy, and postpartum periods. Learnings will target consumers, program facilitators, health professionals, services, and policy makers to inform future scale up to ultimately benefit the health of women across these life-phases.

**Trial Registration:**

Australian and New Zealand Clinical Trial Registry ACTRN12620001053910; https://www.anzctr.org.au/Trial/Registration/TrialReview.aspx?id=378243&isReview=true

**International Registered Report Identifier (IRRID):**

DERR1-10.2196/33625

## Introduction

### Background

Obesity is a major global public health and economic burden. In an increasingly obesogenic environment, young women are a high-risk population group with suboptimal lifestyle behaviors [1], accelerated weight gain, and rising obesity prevalence across early to middle adulthood [2,3]. Prior to pregnancy, excess weight affects fertility [4] and independently increases the risk of adverse maternal and neonatal outcomes [5]. During pregnancy, up to 50% of women exceed international gestational weight gain recommendations [6], which increases their risk of complications, such as gestational diabetes, cesarean section delivery, and having a large-for-gestational-age infant, compared with those whose weight gain is within recommendations [6,7]. Independent of maternal prepregnancy BMI, excessive gestational weight gain increases subsequent childhood [8,9] and maternal obesity by 3-fold [10]. Excessive gestational weight gain superimposed on preexisting overweight or obesity further exacerbates risks and perpetuates a cycle of weight gain in women across their reproductive lifespan [11].

Pregnancy is a critical window in which maternal health behaviors and lifestyle should be optimized to benefit the future health of both mother and child [11]. Consequently, most research to date has concentrated on efficacy-based antenatal lifestyle interventions for improving outcomes [12,13]. A recent systematic review and meta-analysis [12] by the US Prevention task force of 68 trials that involved a total of 25,789 women reported a reduction in gestational weight gain after behavioral lifestyle interventions (mean difference −1.02 kg, 95% CI −1.30 to −0.75; 55 studies; n=20,090), with an associated reduction in gestational diabetes (relative risk 0.87, 95% CI 0.79 to 0.95; 43 trials; n=19,752) and emergency cesarean delivery (relative risk 0.85, 95% CI 0.74 to 0.96; 14 trials; n=7520) risks [12]. This level 1 evidence on antenatal healthy lifestyle intervention efficacy is supported by findings of cost-effectiveness and potential cost savings [14], mandating translation into policy and practice [12,15].

However, vital implementation gaps remain [16]. Weight management guidelines for preconception and pregnancy periods lack quality, consistency, and translation of effective intervention strategies into practice with extended reach that is in line with real world experience [17]. Barriers in the preconception period include identifying and engaging women who intend to become pregnant and who are, otherwise, not regularly engaged with the health care system [18]. In pregnancy, identifying broad reach, feasible intervention delivery methods, including remote delivery options, remains unclear [12,13]. Barriers in the postpartum period include engagement, penetration, and uptake of healthy lifestyle interventions with very limited reach and impact to date [19]. To leverage the substantial investment in efficacy trials and deliver health impacts, these barriers must be addressed.

We previously designed a low-intensity, low-cost healthy lifestyle program, called HeLP-her, that has engaged thousands of reproductive-aged women and has an extensive evidence base [16,20-24]. The program effectively prevents progressive weight gain in reproductive aged women [22,23], estimated to be between 0.625 kg and 1.2 kg per year [25], depending on the population studied [2,26]. During pregnancy, HeLP-her optimized gestational weight gain (intervention: mean 6.0, SD 2.8 kg; control: mean 6.9, SD 3.3 kg; *P*<.05) and postpartum weight retention (intervention: mean 0.51, SD 4.48 kg; control: mean 1.96, SD 5.74 kg; *P*<.05) overall, with the greatest efficacy demonstrated in nonobese women [20,21,27]. HeLP-her is theoretically underpinned and improves self-management behaviors through health coaching supported by intervention resources and self-management tools. It has been contextually adapted successfully across delivery methods, settings, and life stages, retaining core components to ensure fidelity [16,20,21,23].

Our formative work has included extensive evidence synthesis to systematically evaluate the efficacy of lifestyle interventions incorporating diet, physical activity and weight- and self-management behaviors during preconception [28], pregnancy [13], and postpartum [19] periods, to integrate key intervention components and inform study design. We have developed and integrated health-related content based on best practice clinical guidelines [29,30] and have identified facilitators and barriers to healthy lifestyle– and weight-related behaviors, information preferences, and health professional engagement across these life stages [31-34]. We have engaged consumers and health professionals to iteratively adapt our evidence-based intervention for broader reach, with translation of the intervention content, resources, and tools to a dedicated web-based digital platform, and have performed extensive consumer testing to evaluate and iteratively optimize acceptability, relevance, and engagement of intervention content in a representative target population of women.

### Overall Aim

Applying a hybrid effectiveness-implementation study, we aim to generate key implementation learnings to inform the feasibility of future scale up and determine the effectiveness of intervention delivery methods on engagement, experience, acceptability, knowledge, risk perception, health literacy, and modifiable weight-related health behaviors in women during preconception, pregnancy, and postpartum periods.

### Specific Objectives

Our objectives are as follows:

Determine implementation feasibility with 1) process evaluation (ie, measure of process used to implement the program and any variation experienced; facilitators and barriers to intervening events impacting implementation), 2) the RE-AIM framework to assess Reach, Effectiveness, Adoption, Implementation and Maintenance of the intervention and 3) cost effectiveness analysis.Evaluate intervention participation (ie, engagement and adherence to program) and engagement (ie, degree of online module completion, frequency, and duration of time spent on the platform).Determine intervention effectiveness on health related outcomes measured at the individual level including health knowledge, health literacy, and self-management behaviors.Determine any discrepancy according to the health coaching delivery method.

### Hypotheses

We hypothesize as follows:

The intervention will be feasible to implement and can effectively reach and engage women prior to pregnancy through co-designed strategies that are acceptable to women and the implementation partner with demonstrated cost-effectiveness.Participation and engagement with intervention resources will be greater for participants who complete the intended intervention dose compared with those who do not.The intervention will improve preconception and pregnancy health knowledge and self-management.Phone and videoconference health coaching delivery will be equally feasible and cost-effective, yet engagement, adherence, and effectiveness will be greater with videoconference compared with phone-based health coaching.

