#### Health Coaching Sessions

Health coaches with a tertiary qualification in health sciences (ie, dietetics, nutrition, exercise physiology, or allied health) will deliver the program and aim for continuity wherever possible to maintain rapport. The purpose of the individual health coaching sessions is to build rapport with participants, reiterate program objectives, enhance engagement, practice goal setting and self-management skills, support participants with lifestyle modules, and provide personalized feedback on behavior change. Any module components that have not been accessed or completed by participants at the point of health coaching will be flagged for completion by the participant during or after the session.

All participants will be offered 2 personalized preconception health coaching sessions (approximately 20 minutes in duration, delivered either be phone or videoconference according to randomization) 2 to 4 weeks after program entry and 6 weeks later.

During pregnancy, 2 additional 20-minute health coaching sessions will be scheduled (8-10 weeks gestation or 1-2 weeks after starting the pregnancy module commencement and 19-20 weeks gestation).

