### Outcome Measures

Outcome measures (Table 1) are underpinned by the RE-AIM (Reach, Effectiveness, Adoption, Implementation and Maintenance [45]). Both quantitative (recruitment and intervention delivery fidelity checklists [46]) and qualitative (semistructured interviews) data collection methods will be used (Multimedia Appendix 1 and Multimedia Appendix 2).

**Table 1 table1:** Description of outcome measures.

Outcome			Description
**Implementation feasibility (primary)**			Program evaluation and feasibility for future scale up
	Reach	Proportion of the target population that were invited and participated in the program and intervening factors	
	Implementation fidelity	Delivery according to design and any variation experienced Facilitators and barriers: identification and description of intervening events	
	Adoption of the program by the implementation partner	Contextual events or factors influencing implementation within the setting, variation in any co-design implementation component	
	Cost-effectiveness	To answer questions about overall feasibility of implementation	
**Intervention effectiveness (secondary)**			Exploratory evaluation of the effectiveness of intervention delivery across preconception and pregnancy (Figure 1)
	Participation	Adherence and engagement measures to intervention dose including health coaching sessions and web-based platform interaction including degree of module completion, frequency and duration of time spent on the platform	
	Acceptability	A set of questions relating to the influence of the program in changing health behaviors, the usefulness and relevancy of the information provided, valuable aspects of the program and areas for improvement Qualitative data analysis of insights, participation factors, intervention reach, adoption and maintenance of behavior change, intervention delivery format, and areas for improvement until thematic data saturation	
	Effectiveness	On individual health behaviors including self-reported weight, health literacy [47], self-management [48], diet [49], and physical activity [50] using validated questionnaires Collected at the start of the intervention, after preconception health coaching sessions and module, and at the start of the pregnancy module	

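### The participation part of Hypothesis 2 is true by construction: women are grouped by completing the dose, and participation is defined as adherence to that dose

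*Protocol article*

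**What the plan says.** The second hypothesis in the protocol article (Hypotheses) reads: "Participation and engagement with intervention resources will be greater for participants who complete the intended intervention dose compared with those who do not".

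Two other places say what participation and engagement are. The Specific Objectives set out to "Evaluate intervention participation (ie, engagement and adherence to program) and engagement (ie, degree of online module completion, frequency, and duration of time spent on the" platform. The Participation row of Table 1 (Outcome Measures) describes "Adherence and engagement measures to intervention dose including health coaching sessions and web-based platform interaction including degree of module completion, frequency and duration" of platform use.

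The coaching part of the dose is in Health Coaching Sessions: "All participants will be offered 2 personalized preconception health coaching sessions", and then "During pregnancy, 2 additional 20-minute health coaching sessions will be scheduled". The same section says that unfinished module components "will be flagged for completion by the participant during or after the session".

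Only the coaching mode, telephone or videoconference, is randomised (Randomization). Table 1 places participation among the secondary outcomes, under an exploratory evaluation. The Statistical Analysis section sets a general significance threshold of P<.05 and names no specific test for Hypothesis 2.

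**The concern.** A hypothesis is informative only if some result could contradict it. Here women are sorted by whether they completed the dose, and the outcome includes how far they adhered to that dose. To that extent the same behaviour stands on both sides of the comparison.

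Hypothesis 2 is one of four stated hypotheses, and the study is meant to inform scale-up. Reporting it as supported would look like evidence about how participation and dose relate, when the participation part was settled by the definitions. The engagement part may carry real information, but only if the dose excludes the platform measures used to assess engagement. The wording of the article does not keep them apart.

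**Working it through.** The article gives no power or effect figure for Hypothesis 2, so there is none to reproduce. The check has two steps.

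**Step 1: the definitions side by side.**

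- Groups (Hypotheses): women who did or did not complete the intended dose.
- Participation (Specific Objectives): engagement plus adherence to the program.
- Participation (Table 1): adherence and engagement relative to the dose, with coaching sessions and platform interaction both listed.
- Engagement (Specific Objectives): module completion, frequency and time on the platform.

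Suppose the dose is the 2 preconception sessions. Completers attended 2, and non-completers attended 0 or 1. The difference in mean sessions attended is then at least 2 − 1 = 1 and at most 2 − 0 = 2, whatever the data. For illustration, let each session be attended independently with probability p. The mean among non-completers is 2p(1 − p)/(1 − p²) = 2p/(1 + p), so the difference is 2 − 2p/(1 + p) = 2/(1 + p). With an assumed p = 0.7 this is 2/1.7 = 1.18 sessions.

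If the dose also requires platform use, some non-completers may have attended both sessions. The difference in sessions still cannot be negative, and it is positive as soon as one non-completer missed a session.

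**Step 2: which other measures are forced, and under which reading of dose.** A simulation generated sessions attended, module completion, log-ins and minutes as mutually independent, so no true association exists. It used n = 300 (Sample Size), 2,000 runs and a Welch t-test at two-sided 0.05; the article does not state sidedness. These inputs are assumptions: 2 sessions with 70% attendance each, and arbitrary distributions and cut-offs for platform use. Cells give the share of runs with a positive difference / with a positive and significant difference.

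| Measure | Dose = coaching only | Dose = coaching + module completion | Dose = all Table 1 items |
|---|---|---|---|
| Sessions attended | 100% / 100% | 100% / 100% | 100% / 100% |
| Module completion | 49% / 2.4% | 100% / 100% | 100% / 100% |
| Log-ins | 50% / 2.6% | 50% / 2.1% | 99% / 59% |
| Minutes on platform | 49% / 2.4% | 49% / 0.9% | 99% / 53% |
| Equal-weight sum of the four | 100% / 100% | 100% / 100% | 100% / 100% |

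A two-sided 5% test should give about 2.5% positive and significant results when nothing is going on. Under the coaching-only reading the three platform measures behave that way. Once a measure enters the definition of dose, it is pushed upward. The direction for sessions attended follows from the definition. The row for the sum depends on equal weighting, and the 59% and 53% depend on the assumed cut-offs.

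**The case against.** The strongest reply is that Hypothesis 2 speaks of engagement with intervention resources. The Background describes coaching as supported by resources, and the Platform section uses the word for fact sheets and similar material. On that reading the hypothesis says that women who complete their coaching use the platform more, which is an ordinary association that can fail. The coaching-only column of the table bears this out, and the point stands for engagement. It does not rescue participation, because both places that define participation include adherence, and Table 1 lists coaching sessions explicitly.

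A reader might infer that the whole hypothesis will be confirmed whatever happens. The documents do not support that, because the dose may mean coaching only.

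A reader might also count the coach's prompt to finish modules as part of the circularity. It is an intervention mechanism: a prompt does not guarantee completion, and platform use that rises by this route is a real consequence of attending.

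A reader might further infer a fixed four-session dose, under which women who do not conceive, or who conceive early, would count as non-completers. The article does not say this. It offers 2 sessions to all and schedules 2 more in pregnancy. Any figure for how many women would be misclassified would need conception rates and a date of starting to try, and the article gives neither.

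Finally, it can be said that the outcome is exploratory, that no completer test is written down, and that a completion threshold may stand in the full plan. These points limit the weight of the finding. They do not remove it: any dose definition that includes coaching sessions leaves those sessions on both sides for as long as participation counts them.

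**Conclusion.** The point holds for participation. As far as participation counts adherence to the dose, completers must score higher, by 1 to 2 sessions if the dose is the 2 preconception sessions, and confirming this part of Hypothesis 2 would tell the reader nothing.

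For engagement the point is conditional. The comparison is circular if the dose includes platform use, as the Table 1 wording suggests, and open to refutation if the dose is coaching sessions only. Even then it compares groups that women sort themselves into after randomisation, so it shows association and not an effect of dose.

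The conclusion rests on reading participation as the Specific Objectives and Table 1 define it. The weight is moderate: one secondary, exploratory hypothesis is affected. The randomised comparison of telephone with videoconference and the descriptive primary outcomes are not.

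**What to change.** Either of two changes is enough.

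1. **Keep Hypothesis 2 and separate its two sides.** Define dose completion as coaching sessions attended out of those due to the woman under the schedule in Health Coaching Sessions. Compare it only with platform measures outside that definition: module completion, frequency and time. Preferably, use platform activity after the dose window and adjust for activity before the first session. For the preconception sessions, the window should close only after the second falls due, at 2 to 4 weeks plus 6 weeks, that is 8 to 10 weeks after entry. Label the result a non-randomised association. The adjustment reduces self-selection but does not remove it.

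2. **Drop Hypothesis 2 as a test** and report dose and engagement descriptively by arm. Little is lost, because Hypothesis 4 already addresses engagement and adherence through the randomised contrast.

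The cost is minor rewording of the hypothesis and the Participation row of Table 1, and for the first option a little more analysis of platform data that the study already plans to collect.

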## Methods

### Implementation

#### Design

OptimalMe is a type 3 hybrid effectiveness-implementation study [35] with an active intervention phase (2 years) and a passive observation phase (up to 5 years). Type 3 hybrid implementation designs are those in which implementation outcomes are primary, and individual or population outcomes are secondary [35]. The primary outcome of the project includes overall intervention penetration and reach and the feasibility, acceptability, adoption, and fidelity of the delivery of OptimalMe. Secondary outcomes include evaluation of individual health outcomes associated with implementation delivery mode, including knowledge, risk perception, health literacy, self-management, and health behaviors. The study design is a parallel, two-arm, randomized trial at the level of the individual utilizing a pragmatic philosophy, working within real-world conditions to assess overall effectiveness. All individuals will receive the same evidence-based lifestyle intervention, and implementation delivery methods will be compared.

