#### Randomization

Participants will be randomized to receive health coaching either by telephone or via videoconference. An external senior statistician will provide computer-generated randomization codes to the research coordinator only, who will sequentially allocate all participants but will have no role in intervention delivery. Researchers involved in intervention delivery and data collection will be blinded to the allocation sequence; however, due to the nature of the intervention, they will not be blinded to participant allocation. Researchers responsible for data analysis and reporting will be blinded to both allocation sequence and participant allocation. Randomization performed external to the implementation setting is designed to reduce bias. Due to the nature of the intervention, participants will not be blinded to group allocation.

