### Statistical Analysis

Deidentified quantitative and qualitative databases will be maintained on encrypted Monash University servers and managed by research staff involved in data collection. We will use descriptive approaches to evaluate primary outcomes measures. Quantitative data collected for secondary outcome measures will be exported to STATA (version 17.0; StataCorp LLC). Descriptive statistics (means with standard deviations or frequencies with ranges) will be used to characterize intervention effectiveness and the recruited sample by demographic characteristics (age, BMI, country of birth, education, socioeconomic status, and parity), preexisting health, and health-related behaviors (ie, self-management, diet, and physical activity). Logistic and linear regression models will be used to explore associations between before and after the intervention. Additionally, factors known to influence secondary outcomes, including weight, such as diet, physical activity, breastfeeding status, and parity will be adjusted for a priori. Mixed-effects regression models, with the individual specified as the random effect, will be investigated to account for repeated measures. Missing data will be examined, and multiple imputation will be used to generate complete data, if data are not found to be missing at random. Sensitivity analyses will be performed to explore robustness. A *P* value <.05 will be considered statistically significant.

Transcripts of semistructured interviews will be independently analyzed and coded by 2 researchers using NVivo software (version 12; QSR International). Data will be searched for concepts in relation to participatory factors and program evaluation, with codes generated and grouped into themes using an inductive approach. Quantitative data will be analyzed first, to inform thematic analyses. The definitions of themes will be determined by consensus (between 2 researchers).

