## Discussion

Prevention of weight gain and obesity is a global health priority. Increased emphasis is placed on high-risk populations [53,54], including reproductive-age women with accelerated preconception, pregnancy, and postpartum weight gain [6]. Lifestyle interventions can be used to optimize weight and reduce maternal and neonatal adverse outcomes [12,55], yet translation of effective interventions into real-world settings remains critically limited. We address this gap and leverage extensive investments in efficacy research by undertaking implementation research to inform feasibility, acceptability, applicability, effectiveness, and sustainability of an evidence-based weight gain prevention intervention for preconception, pregnancy, and postpartum periods. Implementation research leverages investment in efficacy-based randomized trial knowledge to study methods that promote the systematic uptake of evidence-based interventions into practice and policy to improve health [35].

Our study design aligns with best practice implementation research; focuses on system-level outcomes; and is underpinned by evidence from efficacy trials, systematic reviews, meta-analyses, and guidelines. Additional health information, specific to preconception, pregnancy, and postpartum life stages, has been integrated, with checklists and resources. Evidence on core and peripheral components has been integrated to adapt the intervention with stakeholders across women, multidisciplinary clinicians, and partners. Novel delivery strategies, including sophisticated digital platform and remote health coaching delivery methods, while retaining core intervention features including low-intensity individual health coaching and ongoing text message support. This work has integrated, and been supported by, robust implementation and intervention frameworks and theories.

We anticipate that the OptimalMe intervention will demonstrate feasibility and directly provide evidence to inform scaled intervention delivery. Learning will not only inform future implementation design but translation of evidence targeting consumers, program facilitators, health professionals, services, and policy makers to inform future scale up of healthy lifestyle interventions to ultimately benefit the health of women.

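### Objective 3 and hypothesis 3 claim an effect of OptimalMe itself, but both arms receive it and the overall analysis is an uncontrolled before-after comparison

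*Protocol article*

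**What the plan says.** All statements are in the protocol article.

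- **Objective and hypothesis.** The third item under Specific Objectives is: "Determine intervention effectiveness on health related outcomes measured at the individual level including health knowledge, health literacy, and self-management behaviors". The matching item under Hypotheses is: "The intervention will improve preconception and pregnancy health knowledge and self-management". Delivery mode has its own separate objective and hypothesis (the fourth in each list), so the third concerns the program as such.
- **Who gets the program.** Implementation, Design: "All individuals will receive the same evidence-based lifestyle intervention, and implementation delivery methods will be compared". Randomization: "Participants will be randomized to receive health coaching either by telephone or via videoconference".
- **Analysis.** Statistical Analysis gives descriptive statistics and then: "Logistic and linear regression models will be used to explore associations between before and after the intervention". It adds covariate adjustment, mixed-effects models for repeated measures and a significance level of P<.05. No untreated group, historical comparator or benchmark is attached to any individual-level outcome.
- **Outcomes and timing.** The effectiveness row of Table 1 reads: "On individual health behaviors including self-reported weight, health literacy [47], self-management [48], diet [49], and physical activity [50] using validated questionnaires". Collection is at entry, after the preconception coaching and module, and at the start of the pregnancy module. Table 1 calls this evaluation secondary and exploratory.
- **Weight.** The Discussion calls OptimalMe an "evidence-based weight gain prevention intervention for preconception, pregnancy, and postpartum periods". The Background says of the parent program: "The program effectively prevents progressive weight gain in reproductive aged women [22,23], estimated to be between 0.625 kg and 1.2 kg per year". No outcome or analysis uses that rate.

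**The concern.** An effect of the program is a contrast between what happens with it and what would have happened without it. The trial observes only the first. Hypothesis 3 therefore rests on each woman's change since entry, and any change that would have occurred anyway is counted as effect.

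The population makes such change plausible. Under Eligibility Criteria and Recruiting Strategy, participants joined or upgraded to pregnancy cover within the previous 3 months, wish to conceive within 12 months, and opted in. Under Platform, the pregnancy module opens when a woman enters her pregnancy status and due date, so the last listed measurement is tied to becoming pregnant. Pregnancy is itself a plausible prompt to learn and to change behavior.

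Weight raises a related problem of interpretation. If the aim is to prevent gain, success in non-pregnant women looks like no change, and a test against zero cannot recognise it.

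At stake is whether uncontrolled change is reported as demonstrated effectiveness of OptimalMe.

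**Working it through.** **1. Claim against design.** The claim needs OptimalMe versus no OptimalMe. The randomised contrast is telephone versus videoconference within OptimalMe. It is protected from background change, because both arms share that change, but for the same reason it carries no information on the program's own effect. Covariate adjustment and a random effect for the individual deal with between-woman differences and correlated measurements. Neither supplies a comparator.

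**2. Sample size.** The article states no power or effect size for these outcomes. Its one figure is that 300 women are about 10% of the eligible population intending to conceive: 300/(7800 × 0.41) = 300/3198 = 9.4%, which agrees at that rounding. I use n = 300 below.

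**3. Background improvement in knowledge or self-management.** Assume the program has no effect and the mean score rises by d standard deviations of the change score. With a two-sided 5% test (sidedness is not stated, so this is assumed), the probability of a significant improvement is approximately Φ(d√n − 1.96). The values of d and the 200 completers are assumptions.

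| d | n = 300 | n = 200 |
|---|---|---|
| 0.10 | 0.41 | 0.29 |
| 0.15 | 0.74 | 0.56 |
| 0.20 | 0.93 | 0.81 |
| 0.30 | >0.99 | 0.99 |

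Example: d = 0.20, n = 300 gives 0.20 × 17.32 − 1.96 = 1.50, and Φ(1.50) = 0.93.

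**4. Non-pregnant weight.** Health Coaching Sessions places the second preconception session 6 weeks after one held at 2 to 4 weeks, so about 8 to 10 weeks from entry. Untreated gain = annual rate × weeks/52:

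- low: 0.625 × 8/52 = 0.10 kg
- high: 1.2 × 10/52 = 0.23 kg

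The article gives no SD for this weight change. I take 2 to 5.74 kg as an assumed range; the upper end is the SD of postpartum weight retention among controls in the earlier program (Background). The 95% half-width is 1.96 × SD/√300:

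| SD (kg) | Half-width (kg) | Annualised, 10 weeks (× 52/10) | Annualised, 8 weeks (× 52/8) |
|---|---|---|---|
| 2 | 0.23 | 1.2 kg/year | 1.5 kg/year |
| 5.74 | 0.65 | 3.4 kg/year | 4.2 kg/year |

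If gain is fully prevented, the true change is 0 and the before-after test is significant 5% of the time. If the program does nothing, the test shows a significant change with probability 0.06 to 0.13 at a gain of 0.10 kg and 0.11 to 0.52 at 0.23 kg, over the same SD range. A non-significant result is therefore expected under full success and common under complete failure. It does not distinguish the two.

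**The case against.** The case for the plan is substantial. The absence of an untreated arm is a deliberate type 3 hybrid choice, with efficacy evidence taken from earlier trials. Table 1 labels effectiveness secondary and exploratory, and the regressions are said to explore associations. The Overall Aim speaks of the effectiveness of delivery methods, and Implementation, Design ties the secondary outcomes to delivery mode. An analysis plan that is not shown might govern interpretation. All of this limits the weight of the point, and none of it calls for a control arm. But the third objective and hypothesis go beyond the article's own framing, and an analysis plan cannot create the missing comparator.

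Stronger readings are tempting and are not supported:

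- **That the plan will score zero weight change as failure.** Neither objective 3 nor hypothesis 3 names weight, and the article nowhere says that a null test means no effect or that a gain means harm. Weight is one item in a secondary outcome row.
- **That gestational gain will swamp the effect.** A reader might set the earlier trial's 6.0 kg gain with the program against its 0.9 kg difference from control (6.9 − 6.0). In this trial the listed weight collection stops at the start of the pregnancy module. Later pregnancy weights are not a listed outcome; the platform's gestational weight gain calculator is not described as outcome data.
- **That weight can mislead in one direction only.** Weight is self-reported by women who opted in while planning a pregnancy, so background loss or reporting drift could also favor the program.
- **That an upper confidence limit below 0.625 kg/year could define prevention.** With zero observed change and an SD of 2 kg, that limit is already 1.2 to 1.5 kg/year, so a fully effective program would fail.
- **That these results would drive the scale-up conclusion.** Table 1 attaches scale-up to the primary implementation outcomes.

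**Conclusion.** The point holds for objective 3 and hypothesis 3 as worded. The design cannot separate an effect of OptimalMe on knowledge, health literacy or self-management from background change, and a modest drift would often pass P<.05: probability 0.41 to 0.93 for an assumed 0.10 to 0.20 SD with 300 women. The probabilities depend on the assumed drift and number of completers. The conclusion about the design does not.

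For weight the point is narrower. Over 8 to 10 weeks the expected untreated gain is only 0.10 to 0.23 kg, no larger than the 95% half-width even at an SD of 2 kg, so the before-after test says little either way. The rate of 0.625 to 1.2 kg/year varies by population, according to the Background, and is not established for this cohort.

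The primary implementation outcomes and the randomised delivery-mode contrast are unaffected. This should be changed, but it does not threaten the trial.

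**What to change.** 1. Reword objective 3 and hypothesis 3 as describing change from entry in knowledge, health literacy and self-management among OptimalMe users, reported as estimates with 95% confidence intervals.
2. State that only the randomised telephone-versus-videoconference contrast supports a causal claim. This agrees with the Overall Aim and with Implementation, Design.
3. For self-reported weight, say in advance that a non-significant before-after test will not be read as no effect, nor a gain as harm. Report non-pregnant change with its 95% confidence interval, descriptively, beside the 0.625 to 1.2 kg/year in the Background, scaled to the actual interval. Set no pass/fail threshold, because 8 to 10 weeks is too short for a precise rate.
4. Do not interpret a weight taken in pregnancy as an effect of the program.

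The cost is the wording of one objective and one hypothesis plus one descriptive presentation, with no new data. The downside is a weaker claim about what the program achieves.
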